## Abstract

**Background:**

There is scarce knowledge on the use of structured positive psychology interventions for reducing work-stress and improving wellbeing of rural community health workers in India, particularly the Accredited Social Health Activists (ASHAs) who are village-level (resident women, incentivised) lay health workers. This trial will test the effectiveness of a ‘character-strengths’ based coaching intervention compared to routine supervision on wellbeing (‘authentic happiness’) of ASHAs.

**Methods:**

This protocol is for a single-blind, parallel group randomized controlled trial comparing the effectiveness of a five-day residential workshop focusing on the use of character-strengths and subsequent 8- to 10-week remote telephonic coaching (weekly) to individually support ASHAs to improve their wellbeing, against routine health system support. The arms are intervention added to routine ASHA supervision (weekly, by the ASHA supervisor), and routine supervision alone (control arm). The target sample comprises 330 rural ASHAs in Madhya Pradesh, India. The primary outcome of mean Authentic Happiness Inventory (AHI) scores will be compared between arms at 3-month follow-up. Secondary outcomes will include an assessment of ASHA's self-reported affect, self-efficacy, flourishing, burnout, motivation, physical health symptoms, quality of life, and routine work performance indicators, and the consequent patient-level outcomes [e.g., service satisfaction and depression remission rates after receiving brief psychological treatment by trained ASHAs]. We will also evaluate the costs of developing and delivering the intervention.

**Discussion:**

This trial will determine whether a character-strengths based coaching intervention is an effective and scalable approach for reducing work-stress and improving wellbeing of rural ASHAs in low-resource settings.

## Introduction

1

Community Health Workers (CHWs) in low-resource settings experience high levels of work-stress [1,2], while serving the communities they live in, and bridging their health needs [[3], [4], [5]] with formal health system outlets such as primary care clinics. Accredited Social Health Activists (ASHAs) in India are one such cadre and play a significant role under the National Health Mission (NHM) to strengthen the delivery of primary health services in rural communities [6]. In India, there is typically one ASHA (woman, resident) per village (for a population of ∼1000) who receives an initial 23-day training on linking community members to basic health services, providing basic first aid and supplies, and mobilizing the community around water, sanitation, nutrition, and health issues [7]. There are more than a million ASHAs selected and trained in India, making it one of the largest CHW programs in the world [7].

ASHAs are vulnerable to work-related stress, contributed by unequal workload distribution [8,9] and gender inequities within the health system [10]. Prior studies have reported low compensation relative to work demands, and dependence on incentives compared to other salaried personnel with whom they work (such as Auxiliary Nurse Midwives), in addition to delays in receiving performance-based incentives, poor institutional support, inadequate respect from seniors and peers [11], and limited voice to express their concerns being at the bottom of health system hierarchy [12]. On the other hand, patriarchal values embedded within households and the wider village community, family expectations around gendered domestic responsibilities, low socioeconomic status, poverty, and limited education contribute to individual-level stress [8,10].

While addressing these issues will need continued structural changes at multiple levels of the health system and the society at large, the potentially more immediate solutions aimed at promoting mental health and well-being of ASHAs are worth examining. There is a scarcity of studies addressing stress among CHWs in LMICs such as India [1], and prior work has generally focused on improving the ‘external’ factors such as monetary incentives, supervision strategies, task-allocation and flexibility, public recognition, and rewards, with inadequate attention to ‘intrinsic’ factors such as mental health, coping abilities, and wellbeing of ASHAs themselves [13].

In this respect, the personal attributes or strengths of an individual may influence the negotiation with work-stress. Cross-sectional studies indicate positive associations between specific ‘character-strengths’ (e.g., inquisitiveness or gratitude) and psychological well-being among the nursing cadres [14,15], who are similar to ASHAs in their job roles, with the mediating effects of social support and self-efficacy [15], or engagement in work [16]. Recent experimental evidence among nurses has also shown that interventions, combining the use of character‐strengths with mindfulness-based practices, have reported higher absolute scores of ‘hedonic’ (pleasure-attainment) and ‘eudaimonic’ (meaning and self-realisation) well‐being, than exclusively mindfulness-focused interventions [17].

Keeping rural ASHAs in mind, there is scarce knowledge of the use of such intervention models through experimental designs for improving wellbeing, and an absence of longitudinal studies and randomized controlled trials [18]. Further, the typical approach of ‘identify and use’ the strengths in challenging situations, adopted by studies in other global settings [19,20] (with more educated and privileged workplace employees in high-income regions) would need substantial contextual adaptation for CHWs such as ASHAs in India, as shown in our process of development of the proposed intervention [13].

### Study objectives and hypothesis

1.1

The objective of this two-arm randomized controlled trial is to compare the effectiveness of a character-strengths based coaching intervention on wellbeing of ASHAs relative to routine health system supervision that ASHAs already receive.

The hypotheses include:A)Primary hypothesis: ASHAs who receive the proposed coaching intervention (in addition to routine supervision) will show greater wellbeing than those who receive routine supervision alone.B)Secondary hypotheses:a)ASHAs who receive the proposed coaching intervention (in addition to routine supervision) will show greater reduction in burnout and increase in motivation scores, than those who receive routine supervision alone.b)ASHAs who receive the proposed coaching intervention will show greater improvement in service delivery indicators (e.g., daily service contacts for routine services such as prenatal check-ups and conducting brief psychological treatment sessions for depression) than those who receive routine supervision alone.c)ASHAs who receive the proposed coaching intervention will show greater patient satisfaction for depression care services, and rates of remission in their patients' depression severity at endpoint, than ASHAs who receive routine supervision alone. (Note: All ASHAs prior to baseline assessment will be trained to deliver the brief psychological treatment for depression, see Fig. 1)

**Fig. 1 fig1:**
[figure not shown]
Trial CONSORT diagram.

## Methods

2

### Study design

2.1

This study will have a two-arm single-blind parallel randomized controlled trial design with equal allocation of participants (ASHAs) between arms (Fig. 1). ASHAs in the control arm will be supported by their routine ‘ASHA facilitators or supervisors’ who typically supervise a group of ∼20 ASHAs on a weekly basis.

### Study setting

2.2

This trial will be conducted in Sehore district in the state of Madhya Pradesh (MP) in central India. Being one of the largest states of India, MP has a population of over 72 million, nearly 73 % of whom live in rural areas [[21], [22], [23], [24], [25], [26], [27]] and it lags other Indian states with respect to human development and availability of resources [23,28]. About ∼1300 rural ASHAs work in Sehore district and as part of the study team's earlier trial, ∼330 ASHAs were trained to deliver an evidence-based brief psychological treatment for depression i.e., the Healthy Activity Program (HAP) [29].

### Study procedures

2.3

#### Participant recruitment

2.3.1

The trial will include Accredited Social Health Activists (ASHAs), working at the intersection of primary care and community levels, and currently not receiving any structured evidence-based coaching in improving their wellbeing and/or coping with work-stress [Note: We use the term ‘work-stress’ to indicate overall stress experienced by an ASHA, contributed by workplace, domestic (home/family environments) and village-level (her work in the community through house-to-house visits and village-level healthcare activities) stressors.]

Recruitment will start with the research coordinator and study data manager compiling a list of ASHAs from all blocks in Sehore district with the support of the District Program Manager, National Health Mission, and Block Medical Officers. This list will form the sampling frame for the trial. From the sampling frame, we will exclude ASHAs who have participated in mental health trainings, which could potentially equip them with mental health knowledge and techniques to manage their work-stress/burnout [30]. Finally, we will exclude ASHAs who have been a part of formative focus group discussions to develop the intervention for the present trial [31] and ASHAs who participated in the content testing phase of the intervention [13].

We have defined the ASHA selection criteria as follows:

*Inclusion criteria for ASHAs:* All rural ASHAs residing and working in Sehore district, Madhya Pradesh (verified in the health system records) who have been trained on delivering the evidence-based brief psychological treatment for depression [29] will be included in the trial. *Exclusion criteria for ASHAs:* a) ASHAs who plan to migrate within six months of recruitment and b) ASHAs who do not plan to continue working, or those who have resigned or planning to change jobs within six months of recruitment.

We have also defined the selection criteria for patients who will receive depression care by the ASHA, in the course of their routine work.

*Inclusion criteria for patients:* All persons identified by the ASHA in the community with a score of 10 or above on the nine-item Patient Health Questionnaire [32] who consent to participate in the trial. *Exclusion criteria for patients:* a) children and adolescents (10–19 years of age as defined by WHO), b) patients with significant speech, hearing, language or cognitive impairment, c) patients needing urgent medical or psychiatric attention, d) patients not planning to stay in the trial location for at least 3 months after initial screening, and e) patients not understanding Hindi.

#### Participant training on the evidence-based brief psychological treatment for depression

2.3.2

In the sampling frame, we will sample a target of 330 ASHAs for orientation and training on the Healthy Activity Program (HAP), an evidence-based brief psychological treatment for community-based care for people identified with depression [29]. We will use simple random sampling (SRS) without replacement for this purpose. SRS will offer maximum sample diversity, equal chance of representation of all ASHAs, high internal and external validity and ease of data analysis [33,34]. This is about 25 % higher than the required number of ASHAs (n = 244, refer 2.6) to account for potential attrition/loss to follow-up and health workers who may decline to participate in HAP training and/or further study processes i.e., baseline assessments, intervention activities and outcome assessments (Fig. 1). The sampled ASHAs will be assigned unique participant IDs, which will be used to contact them regarding trial recruitment. These IDs will stay with the ASHAs throughout the trial period. The research team will call the sampled ASHAs from the list to invite them to participate in the study, starting with an in person orientation on the digital training platform [29] and training for delivering the HAP. After orientation and training completion, ASHAs will start community screening for depression and delivery of 6–8 HAP sessions (every ∼8–15 days) for each patient. ASHAs will also receive fortnightly peer group supervision for the delivery of HAP as documented in previous contextual studies [29,35]. A dedicated team of HAP supervisors, through the MindScroll Learning Management System [36], will supervise the ASHAs’ challenges in delivering HAP, and also retrieve the data on delivery of HAP sessions.

#### Baseline assessment

2.3.3

ASHAs who have completed HAP training, delivered HAP sessions to patients, and received peer group supervision for their delivered HAP sessions, will be invited to come to their nearest community/primary health center to participate in a group information session. A trained research team member will explain the goals of the study to the group and what their participation will involve, depending on the (subsequent) arm allocation. We will provide an overview of the time required to participate in either of the experimental conditions (intervention or control arm) and the completion of study outcome assessments. ASHAs who are interested and willing to participate will meet with a research assistant, who will confirm eligibility and review a study information sheet and consent form with them. The research assistant will ensure that the ASHA has fully read and understood the participant information sheet and consent form before obtaining written informed consent. We will document the number of ASHAs who are eligible to participate, who decline participation (with reported reasons) and who are lost to follow-up.

After consenting, ASHAs will complete the baseline assessment. A research assistant will collect demographic information (including, for example, age, years of work experience, education level, and ownership of assets), and participants will self-report the primary outcome of wellbeing (i.e., authentic happiness), and additional measures (i.e., ASHA's affect, self-efficacy, flourish, burnout, motivation, physical health symptoms and quality of life). The baseline assessment will require approximately 2–3 h to complete. ASHAs will take short breaks at any time during the assessment and will be provided with snacks. The research assistant will be present throughout the process to respond to queries and ensure that ASHAs are able to complete the assessment forms.

From the standpoint of patient recruitment, all patients (of both arms) who score ≥10 on the nine-item Patient Health Questionnaire (PHQ-9) and have agreed to receive the first HAP session by the ASHA will be approached for participation in the study, and after obtaining written informed consent, the research team member will administer the baseline assessment (i.e., social and demographic information) to the patient. We will use the PHQ-9 score as assessed by the ASHA prior to starting HAP as the ‘baseline’, and the endline assessment including a repeat PHQ-9 and assessment of patient satisfaction, conducted by the research assistant after 3 months, will allow a comparison of pre- and post-HAP PHQ-9 scores, in addition to between-arm comparison of remission rates at follow-up.

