### Blinding

2.5

Research coordinators and research assistants administering study assessments to ASHAs and patients, will be blind to participant allocation, and study investigators (except data manager) will also be blind to participants’ experimental condition. Participants will be told their arm allocation only after consent and baseline assessment. There is complete separation between the team members involved in developing or delivering the intervention and assessing intervention fidelity and process indicator data (2.3.5.2 and 2.4.4), and the team members involved in administering the outcome assessments (2.4.1 to 2.4.3). Outcome team members and investigators will be unblinded after the completion of analysis of data of baseline, 1-, 3- and 6-month follow-up assessments.

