### Statistical analysis

2.8

All outcome analyses will be intention-to-treat using imputation of missing outcome data by an appropriate method [60]. The primary outcome analysis will estimate the difference in the mean happiness score between ASHAs randomized to the coaching intervention versus routine supervision at baseline, and 3 and 6 months thereafter. We will assess moderation of coaching effect by *a priori* moderators (e.g., ASHA's age, education status and years of community experience) by fitting appropriate interaction terms and testing for heterogeneity of coaching effects in regression models. We will also assess the relationships between ASHA-level affect, self-efficacy and flourishing, and their more extrinsic outcomes such as authentic happiness, burnout, motivation, physical symptoms and quality of life, and the relationships between these extrinsic outcomes and their service delivery measures, patient satisfaction (of patients receiving depression care) and patient depression remission rates, by a combination of descriptive analyses, statistical tests of significance, and mediation analysis using the MacKinnon's approach [61]. From a patient outcome standpoint, we will compare the remission rates on PHQ-9 of patients between the arms at 3 month follow-up using the test of difference between two independent proportions.

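### For patients entered after allocation, an unblinded ASHA decides PHQ-9 eligibility with no independent baseline score, and the between-arm remission test is unadjusted

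*Protocol article*

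**What the plan says.** **Entry.** Under Participant recruitment (2.3.1), eligible patients are "All persons identified by the ASHA in the community with a score of 10 or above" on the PHQ-9.

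**Baseline.** Section 2.3.3 takes the ASHA's own rating as the patient baseline: "We will use the PHQ-9 score as assessed by the ASHA prior to starting HAP". A member of the research team also sees the patient for consent, but the content of that contact is limited: "the research team member will administer the baseline assessment (i.e., social and demographic information) to the patient".

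**Endline.** The repeat PHQ-9 is "conducted by the research assistant after 3 months". Section 2.5 states: "Research coordinators and research assistants administering study assessments to ASHAs and patients, will be blind to participant allocation".

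**When the ASHA learns her arm.** Section 2.5: "Participants will be told their arm allocation only after consent and baseline assessment".

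**Timing of patient treatment.** Screening and HAP delivery start after HAP training (2.3.2). Those invited to the ASHA baseline are "ASHAs who have completed HAP training, delivered HAP sessions to patients, and received peer group supervision for their delivered HAP sessions". Randomisation follows (2.3.4). Section 2.3.3 describes study patients as belonging to both arms and gives no entry window relative to their ASHA's randomisation.

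**Analysis.** Remission is a 3-month score below 10 (2.4.3, 2.6). Section 2.8 compares it between arms "using the test of difference between two independent proportions".

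**The concern.** The units randomised are ASHAs, not patients. Randomisation therefore protects the patient comparison only if patients enter in the same way in both arms. For a patient entered after allocation, the person who chooses whom to screen, and whose rating decides whether 10 is reached, knows her arm. She must know it, because the arms differ by a five-day residential workshop and weeks of coaching calls.

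The plan's own hypotheses give a reason to expect different behaviour. Secondary hypotheses (a) and (b) in section 1.1 predict higher motivation and more service activity, HAP sessions included, among coached ASHAs. If they screen more widely, or score borderline cases differently, the arms will differ in entry severity. Remission is simply a score below 10 at 3 months, so a patient near or below 10 at entry can meet it without better care. Blinding the endline assessor does not undo selection at entry, and an unadjusted test passes it straight into the result for secondary hypothesis (c).

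Patients who began HAP before allocation raise a different problem. Their selection could not depend on arm, but part of their care predates the coaching, so they tend to dilute a true effect. The article does not say which of these patients count.

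**Working it through.** **1. The plan's own figure.** Inputs from section 2.6: remission 40% against 60%, two-sided α 0.05, 80% power. With p̄ = 0.50:

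n = [1.960·√(2·0.50·0.50) + 0.842·√(0.40·0.60 + 0.60·0.40)]² / 0.20² = 96.9, that is 97 per arm.

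The stated 97 reproduces (pooled variance, no continuity correction; power at 97 is 80.0%). The sample size is not in dispute.

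**2. Which rater enters which comparison.**

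| Comparison | Rater at entry | Rater at 3 months | Effect of a constant ASHA–assistant scoring gap |
|---|---|---|---|
| Pre/post PHQ-9 (2.3.3) | ASHA | Research assistant | Distorts the change score |
| Remission between arms (2.8) | ASHA, through eligibility only | Blinded research assistant, both arms | Same in both arms; no bias in the contrast |

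The arm contrast is biased only if selection or scoring at entry differs by arm.

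**3. Who is exposed.**

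| Patient starts HAP | ASHA knows her arm at entry? | Issue |
|---|---|---|
| Before her randomisation (2.3.2, 2.3.3) | No | Part of care predates coaching |
| After she is told her arm (2.5) | Yes | Eligibility and baseline set by an unblinded recruiter |

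**4. Illustrative size.** Assumptions not in the documents: no treatment effect, 40% remission among ordinary entries in both arms, and a share f of intervention-arm entries who are extra patients truly below 10, of whom a proportion q score below 10 at endline. Then

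p₂ = 0.40·(1 − f) + q·f, and the spurious difference is p₂ − 0.40 = f·(q − 0.40).

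Rejection rate of the two-sided pooled test at 97 per arm, with d = p₂ − 0.40: Φ[(d − 1.96·SE₀)/SE₁] + Φ[(−d − 1.96·SE₀)/SE₁], where SE₀ uses the pooled proportion and SE₁ the two separate ones.

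Worked case, f = 10%, q = 0.9: p₂ = 0.36 + 0.09 = 0.45, d = 0.05, SE₀ = 0.0710, SE₁ = 0.0709. The rate is Φ(−1.257) + Φ(−2.668) = 0.104 + 0.004 = 0.108.

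| f | q | p₂ | Spurious difference | False-positive rate |
|---|---|---|---|---|
| 0 | any | 40% | 0 | 5.0% |
| 10% | 0.8 | 44% | 4 points | 8.7% |
| 10% | 0.9 | 45% | 5 points | 10.8% |
| 10% | 1.0 | 46% | 6 points | 13.4% |
| 20% | 0.8 | 48% | 8 points | 20.1% |
| 20% | 0.9 | 50% | 10 points | 28.7% |
| 20% | 1.0 | 52% | 12 points | 38.8% |

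To mimic the whole planned 20 points, f = 0.20/(q − 0.40), which is 50% at q = 0.8 and 33% at q = 1.0.

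**5. The opposite direction.** Let the planned 60% hold in the intervention arm and put the extra entries in the control arm. With f = 10% and q from 0.8 to 1.0, control remission becomes 44–46% and the difference falls to 14–16 points. Power at 97 per arm drops from 80% to between 50% (q = 1.0) and 61% (q = 0.8).

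**The case against.** **The rater.** A reader might infer that remission could differ between arms merely because ASHAs rate at entry and assistants at endline. The documents do not support that. Remission is an endline score from an assistant blind to allocation in both arms, so a constant scoring gap cancels. This objection stands in full; only the pre/post comparison is affected.

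**Universal unblinding.** A reader might also infer that every patient is recruited by an ASHA who knows her arm. Sections 2.3.2 and 2.3.3 place some screening and HAP delivery before randomisation, so those entries are free of this selection. This stands too, and the point is limited to patients entered after allocation.

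**Size and direction.** Nothing in the article shows that coached ASHAs screen or score differently, and they might enter more severe patients, which would work against the intervention. This is correct. The figures above are illustrations, not estimates.

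**Dropping early starters.** Restricting the analysis to patients who start HAP after randomisation would keep exactly the group open to selection. It would not fully remove dilution either: the workshop comes within 7–10 days of baseline, and calls begin a week after it. This stands, so neither group should be dropped.

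**Left to other documents.** Covariate adjustment of a secondary outcome is often left to a statistical analysis plan, an entry window may be fixed in the full protocol or the flow diagram, and baseline characteristics by arm are already planned for ethics reports (2.9). That is fair for the entry window. It does not answer the choices the article does state: the baseline rater, the content of the patient baseline contact, and the unadjusted test.

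**Conclusion.** The point holds for one secondary outcome and for patients entered after allocation. For them, an unblinded ASHA controls screening and the threshold score, no independent PHQ-9 exists to show or correct an imbalance, and the stated test makes no adjustment. The remission result for secondary hypothesis (c) could be inflated or masked. On the stated assumptions, 10% extra sub-threshold entries in one arm give a spurious 4–6 points, and 20% give 8–12 points, against a planned 20. Whether any such imbalance will arise cannot be known from the article.

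The unspecified entry window is a related but separate weakness: early starters are free of this selection but received some care before the coaching. The primary AHI comparison is not touched. The changes are worth making because they are cheap.

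**What to change.** 1. Have the blinded research assistant administer the PHQ-9 at the existing patient consent and baseline contact, before the first HAP session where feasible. Use that score as the baseline for the pre/post comparison and as the covariate, with the ASHA score as fallback for patients already enrolled. Keep all enrolled patients in the main analysis and use assistant-confirmed scores of 10 or more as a sensitivity analysis, so no patients are lost from the main comparison. Cost: a few minutes per contact and some scheduling.
2. In section 2.8, replace the two-proportion test with a remission model adjusted for baseline PHQ-9 that allows for clustering by ASHA, since an ASHA may contribute more than one patient. Cost: wording only. Adjustment deals with measured entry severity, not with every form of selection, and it is weaker where only the ASHA's score is available.
3. Record each patient's HAP start date relative to the ASHA's randomisation, and present remission separately for patients starting before and after it, without excluding either group.
4. Report by arm the numbers screened, the numbers positive and the mean baseline PHQ-9.

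Enrolment was expected to finish by June 2024 (3.1). If it is complete, items 2 to 4 remain possible from the ASHA scores and whatever HAP session and screening records are held.
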